## Abstract

**Goal::**

The researchers will verify the effects of low-level laser therapy (LLLT) on OSA, when applied to the soft palate and on the tongue base.

**Methods::**

The researchers will select individuals of both sexes aged 30 to 60 years old who are sedentary and that present a high risk of OSA by the Berlin questionnaire. The evaluations pre and post interventions will be polysomnography; anthropometric and body composition measurements (Bioimpedance); metabolic syndrome risk factors (International Diabetes Federation); physical capacity (VO_2_ peak at the cardiopulmonary exercise test, CPET); endothelial function (flow-mediated dilatation, FMD); autonomic control (heart rate variability and sympathovagal balance). Those diagnosed with moderate and severe OSA (apnea/hypopnea index, AHI ≥15 events/h) will be invited to participate in the study and they will be randomized into 2 groups: LLLT treatment or placebo (C). The LLLT group will receive applications at 8 points on the soft palate and on the base of the tongue for 8 seconds for each point. The applications of LLLT will occur twice a week, with a minimum interval of 2 days between the applications for 2 months, when using a Therapy Plus NS 13678 Laser. The C group will have similar applications, but with the device turned off.

**Expected Results::**

In the individuals with OSA, photobiomodulation through LLLT will decrease the AHI. Additionally, when LLLT is applied in the oral cavity, a highly vascularized region, this may cause improvements in the vascular function and in the autonomic and hemodynamic control.

**Ethics and Dissemination::**

This protocol was approved by the Research Ethics Committee of the Nove de Julho University, São Paulo, Brazil, on the date of March 11, 2019 (CAAE: 06025618.2.0000.5511 - Acceptance Number: 3.191.077). This trial has been registered with the Brazilian Registry of Clinical Trials (REBEC TRIAL RBR-42v548). This study is not yet recruiting. Issue date: November 4, 2019.

## Introduction

1

Biophotonics has many possibilities of acting in medicine. Previous studies in animal experimentation^[1]^ and in humans have shown that low-intensity laser therapy interferes positively with healing, inflammation, and oxidative stress,^[2]^ besides provoking analgesia.^[3]^ Additionally, recent studies have pointed to the possibility of high and medium intensity laser therapy in the treatment of patients with obstructive sleep apnea (OSA).^[4]^ This infers that a few applications of this therapy are sufficient to cause an increase in collagen in the soft palate of the patients, a region more susceptible to collapse during sleep. However, in the applications of high and medium intensity laser, the limit between provoking benefits and injuring the sensitive area that is constituted by the mucosa makes it difficult to investigate, especially if it is a future therapeutical application. In this sense, photobiomodulation with clinically applied LLLT may be a safe option for the treatment of snoring and OSA.

The gold standard for the diagnosis of OSA is polysomnography, whereas the treatment is positive airway pressure (CPAP) therapy.^[5]^ However, it is an expensive treatment and it is not covered by the public health service. In addition, several patients do not adapt to CPAP, or even to the intraoral device, while at the same time, they do not consistently adhere to the physical training. These patients, in particular, may benefit from a new therapy. In fact, although CPAP has proven its effectiveness, it is a palliative treatment. In this sense, LLLT, if it proves to be efficient, could be an adjuvant therapy to the conventional treatments with CPAP and the intra-oral device. LLLT may be a new therapeutical option that is safe, easy to apply, and inexpensive (when compared with CPAP and even intra-oral). In addition, it has been demonstrated in mice that LLLT in the vascularized region increases the parasympathetic activity, generating a deceleration of the heart rate, with a decrease in blood pressure, a decrease in sympathetic nervous activity, and a decrease in blood glucose. There is a strong association of OSA with snoring, obesity, and systemic arterial hypertension (SAH), predisposing these patients to a greater cardiovascular risk.

Thus, in this study, the researchers will test the hypothesis that LLLT, when it is applied to the soft palate, decreases the phallus collapsibility, snoring, and the apnea/hypopnea index. In addition, if it improves the autonomic and hemodynamic control in patients with moderate and severe OSA.

The study's anxiety is to check whether the LLLT parameters of this protocol are sufficient to benefit sleep apnea patients. This protocol was designed based on preliminary studies when using validated questionnaires, polysomnography, and spirometry.

In this study, data from other parameters related to sleep disorders will also be collected, which will be analyzed before and after the treatments, in order to allow for the Brazilian population to use a new approach for snoring and sleep apnea. In this way, the research will be aimed at evaluating and comparing the individuals who snore and who suffer from OSA, when submitted to low-intensity laser photobiomodulation, for 2 months over 24 sessions. This will be performed using polysomnography, modified Mallampati, spirometry, and when associated with the questionnaires of Berlin, the Epworth Sleepiness Scale, and the Stress Questionnaire. The groups will be compared, in order to analyze the possibilities of improvements in snoring, apnea, the hypopnea index, the autonomic and hemodynamic conditions, and the blood inflammatory markers when snoring and with OSA. This will be so as to enable the use of this low-intensity laser photobiomodulation in clinical and outpatient practices.

## Method

2

### Study design

2.1

This will be a clinical, randomized, comparative, and blind study. There will be 36 patients randomized into 2 treatment groups: LLLT treatment or placebo (C) (Fig. 1). The study will be implemented over 2 months, divided into 16 sessions, 2 times a week. It will be conducted at the Medicine Outpatient Clinic of the Nove de Julho University, in the city of São Paulo, Brazil. This protocol was written and was based on the Standard Protocol Items: Recommendations for Interventional Trials (SPIRIT). The dissemination and the registration for participation in the study will be carried out through the Nove de Julho University website. The participants will be residents who will mainly be recruited from the city of São Paulo. The participants will be informed about the research, the procedures, the risks, and the benefits by [name] (the author of this protocol). If they agree, they will sign the informed consent form (ICF). Only the participants, who after reading and agreeing to the protocol, and who sign the ICF, will be part of the study.

**Figure 1 F1:**
[figure not shown]
Flowchart of the study.

The study will start in March 2020. The study is not yet recruiting. After the recruitment, the researchers will check if the patients meet the inclusion/exclusion criteria based upon the anamnesis, the Berlin questionnaire, and the polysomnography evaluation.

The patients and/or the public will not be involved in the design, the recruitment, or the conduct of the study. The participants will be men and women who are sedentary, who are not on a diet or drug therapies, and who are at a risk of OSA, by screening with the Berlin questionnaire. Initially, they will perform nocturnal polysomnography. Those diagnosed with moderate and severe OSA (apnea/hypopnea index, AHI ≥15 events/h) will be invited to participate in the study.

### Patient and public involvement statement

2.2

The patients and/or the public will not be involved in the design, the recruitment, or the conduct of the study. The participants will be men and women with moderate or severe obstructive sleep apnea who are sedentary, and who are not on diet or drug therapies.

### Inclusion criteria

2.3

This study will be conducted on men and women aged 30 to 60 years, who are at a risk of OSA, by screening with the Berlin questionnaire. Those patients who have agreed to participate in the study will perform nocturnal polysomnography. Those diagnosed with moderate and severe OSA (apnea/hypopnea index, AHI ≥15 events/h) will be invited to participate in the study.

Subsequently, they will be submitted to clinical/physical examinations, with measurements of demographic and body composition (bioimpedance), as well as with blood pressure and blood tests. The blood samples will be collected from the venous blood after 12 hours of overnight fasting, in order to determine the total serum cholesterol, the triglycerides, the high-density lipoprotein (HDL) cholesterol (enzymatic method), and the plasma glucose (standard glucose oxidase method) concentrations.

### Exclusion criteria

2.4

The participants will be excluded from the survey if they present any of the following:

patients on a diet, on an exercise program, or on drug treatment;pediatric and elderly patients;patients with diagnosed central apnea;smokers;alcoholics;oncologists;pulmonologists;patients with heart disease;hypothyroidism;pregnant women;history of photosensitivity (allergies).

### Sample size calculation

2.5

The sample size was calculated at http://www.openepi.com. It was determined according to an earlier study, with a similar population, displaying metabolic syndrome, and sleep apnea.^[6]^ The primary outcome was a reduction of the AHI. A power of 80% was considered, with a bicaudal type 1 error of 0.05, in order to detect a difference in the AHI of 16 events/h, assuming a standard deviation of 20 events/h.

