### Randomization

2.6

Through the website http://www.randomization.com/, a random block list was generated for the 2 studied groups, LLLT and C. The randomization plan was for 9 blocks of 4 individuals. For both of the groups, the order of the randomization will occur at the entrance to the protocol, by consulting the random list and indicating to which group the patient should be allocated.

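### The inputs in section 2.5 call for 50 to 52 patients by the standard two-group calculation, but the trial randomises 36; at 36, power is about 65% if the SD of 20 is that of the analysed outcome

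*Protocol article*

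**What the plan says.** Section 2.5 (Sample size calculation) of the protocol article says that an online calculator was used, with inputs taken from a cited earlier study in a similar population. The inputs are all printed:

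- power: "A power of 80% was considered";
- significance level: "with a bicaudal type 1 error of 0.05";
- effect and spread: "in order to detect a difference in the AHI of 16 events/h, assuming a standard deviation of 20 events/h";
- outcome: "The primary outcome was a reduction of the AHI".

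The section does not print the resulting number of patients. It does not say whether the SD belongs to AHI at one time point or to its change, and it gives no pre-post correlation.

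The size of the trial appears elsewhere. Section 2.1 says "There will be 36 patients randomized into 2 treatment groups", and section 2.6 confirms it: "The randomization plan was for 9 blocks of 4 individuals", which is 9 × 4 = 36 in total. Section 2.10 plans a repeated-measures ANOVA for the effect of the laser, and section 3 places the measurements before and after the 16 sessions.

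**The concern.** A reader will take section 2.5 as the justification for the 36 patients in sections 2.1 and 2.6, because the article gives no other trial size. The printed inputs do not lead to 36, and the gap is too large for rounding.

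AHI is the primary variable. If 20 is the SD of the analysed outcome, the primary comparison has about a one-in-three chance of missing the effect it was sized for, where the article implies one in five. The article describes the trial as the first randomised evaluation of phototherapy in sleep apnoea, so anyone weighing a non-significant result needs the correct power figure.

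**Working it through.** **Inputs.** From section 2.5: difference δ = 16, SD σ = 20, two-sided α = 0.05 (z = 1.960), power 80% (z = 0.842). From sections 2.1 and 2.6: N = 36. Allocation of 18 per group is inferred from two groups in blocks of 4; unequal allocation would only lower power.

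**1. Sample size from the printed inputs.**
n per group = 2 × (1.960 + 0.842)² × (20/16)² = 24.5, so 25 per group and 50 in total. With the noncentral t-distribution, power is 79.1% at 25 per group and 80.7% at 26, so 26 per group and 52 in total. The figure of 36 is not reproduced; the shortfall is 14 to 16 patients.

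**2. Other readings tried.**

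| Reading | Result |
|---|---|
| One-sided 5% | 40 (normal) or 42 (t) in total |
| Two-sided 10% | 40 in total |
| One-sided 10% | 30 in total |
| Single-group paired formula, SD of change 20 | 13 patients |
| 36 per group | about 92% power, but ruled out by the 9 blocks of 4 |

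None gives 36. Any allowance for dropout would raise the requirement further.

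**3. Power at 18 per group, if 20 is the SD of the analysed outcome.**
Standard error = 20 × √(2/18) = 6.67, and 16/6.67 = 2.40.
- Normal: Φ(2.40 − 1.96) = 67.0%.
- Noncentral t, 34 degrees of freedom: 64.5%.

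**4. What 36 patients can detect with 80% power, on the same condition.**
- Difference: (1.960 + 0.842) × 6.67 = 18.7 events/h (normal), 19.2 (t).
- Largest SD for a difference of 16: 17.1 (normal), 16.6 (t).

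**5. If 20 is the SD of AHI at one time point.** With one measurement before and one after, the group-by-time test of the repeated-measures ANOVA is a t-test on change. Let ρ be the pre-post correlation and assume equal SDs before and after. The SD of change is then 20 × √(2(1 − ρ)). Power at 18 per group (t-test) for assumed values of ρ:

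| ρ | Power |
|---|---|
| 0.3 | 50% |
| 0.5 | 64.5% |
| 0.6 | 74% |
| 0.7 | 85% |

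For 80% power the SD of the analysed outcome must be at most 16.6, and (16.6/20)² ≈ 0.69:
- change comparison: 2(1 − ρ) ≤ 0.69, so ρ of about 0.65 or more;
- ANCOVA: 1 − ρ² ≤ 0.69, so ρ of about 0.56 or more.

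**6. ANCOVA if 20 is the SD of change.** The ANCOVA residual variance is the change variance times (1 + ρ)/2. Then (1 + ρ)/2 ≤ 0.69 gives ρ of at most about 0.38. The direction of the condition reverses, so no ANCOVA threshold can be stated until it is known which SD is meant.

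**The case against.** The strongest objection is that 65% is not a fixed property of this design. It assumes that 20 is the SD of the outcome that enters the test, and section 2.5 does not say so. If 20 is a cross-sectional SD, the planned analysis could have well under 65% power or more than 80%, depending on a correlation that the article does not give. This stands, and it is why the power figure above is conditional. It does not rescue section 2.5, which prints one difference and one SD, relies on no correlation, and so does not lead to 36.

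A second objection is that section 2.5 never claims 36 as its output, and that its inputs come from a cited study not shown here. A mistyped SD is possible: about 16.6 to 17.1 would be consistent with 36. This also stands. The error could lie in an input and not in the number randomised, so the calculator record should be checked before the power is restated.

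A third objection is that a condensed article may leave dropout to the full protocol. That is fair, and the lack of an allowance is not part of this point. The conflict is between figures the article itself prints, and an analysis plan could not make those passages agree as they are worded.

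A reader might also infer that the trial is simply underpowered and must recruit 14 to 16 more patients. The documents do not support this: the inputs may be misreported, or a cross-sectional SD with a high enough correlation may have been intended.

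**Conclusion.** The point holds as an inconsistency in the printed figures. Section 2.5's inputs need 50 to 52 patients by the standard two-group calculation, against 36 in sections 2.1 and 2.6, and no one-sided or per-group reading closes the gap.

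The size of the power loss is conditional. With 18 per group and 20 as the SD of the analysed outcome, power is about 65%. The wording of the primary outcome as a reduction in AHI fits an SD of change, but does not settle it. A reader might take 65% as the trial's actual power; the article does not support that without the condition. That the inputs and the number randomised disagree is certain; which of them is wrong cannot be determined from the article.

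**What to change.** Before recruitment starts, amend section 2.5 as follows.

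1. Check the calculator inputs and output against the cited study, correct any misprint, and print the resulting number of patients.
2. State whether 20 events/h is the SD of AHI or of its change.
3. If 16, 20 and 36 are all confirmed and 20 is the SD of the analysed outcome, state that 18 per group gives about 65% power for 16 events/h, or 80% power for about 19.2 events/h.
4. If 20 is cross-sectional, state the pre-post correlation relied on and its source. For 80% power it must be about 0.65 or more for the planned pre-post comparison, or about 0.56 or more if ANCOVA is adopted.
5. Do not insert the 0.56 threshold without that condition. If 20 is the SD of change, ANCOVA reaches 80% power only with a correlation of at most about 0.38.

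The cost is one paragraph and possibly a less favourable stated power. No extra patients are needed. Section 5 already provides the route: an amendment to the ethics committee and an updated registry entry.

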### Randomization

2.6

Through the website http://www.randomization.com/, a random block list was generated for the 2 studied groups, LLLT and C. The randomization plan was for 9 blocks of 4 individuals. For both of the groups, the order of the randomization will occur at the entrance to the protocol, by consulting the random list and indicating to which group the patient should be allocated.

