#### Epworth sleepiness scale

2.9.4

The Epworth sleepiness scale (ESS) is a questionnaire to detect daytime sleepiness, consisting of a simple subjective scale, and covering 8 different daytime situations. The subjects will be asked to rate on a scale of 0 (those who would never doze) to 3 (high chances of dozing); how likely they would be to doze off or fall asleep in 8 situations, based on their recent everyday life. A distinction will be made between dozing off and simply feeling tired. Thus, the scale will be ranged from 0 to 24, and excessive daytime sleepiness will be defined when the score is ≥11.^[11,15]^

The questionnaire will take a full 10 minutes to be completed. The data that is to be collected for this study will only be administered by the principal investigators (the authors of this document).

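### Assignment by consulting a list in fixed, published blocks of 4, with no concealment step described, leaves about a third of allocations deducible by anyone who knows the earlier ones

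*Protocol article*

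**What the plan says.** Randomization (2.6) reports that "a random block list was generated for the 2 studied groups, LLLT and C", and adds: "The randomization plan was for 9 blocks of 4 individuals". On timing it says "the order of the randomization will occur at the entrance to the protocol", and on method, "by consulting the random list and indicating to which group the patient should be allocated". It does not say who holds or consults the list.

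Study design (2.1) gives a total of 36 patients in two groups and states: "This will be a clinical, randomized, comparative, and blind study". It does not say which roles are blinded. The same section names a single site: "It will be conducted at the Medicine Outpatient Clinic of the Nove de Julho University". Recruitment had not started.

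Interventions (2.8) describes the placebo as the guide light alone with the laser switched off, and places the researchers at the treatment sessions. In the Epworth sleepiness scale section (2.9.4), the data to be collected "will only be administered by the principal investigators (the authors of this document").

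**The concern.** Two separate things are at stake.

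**Allocation concealment, before entry.** If the person judging eligibility knows or can predict the next arm, the decision to enrol, defer or decline a candidate can depend on it, even without intent. Sections 2.1 and 2.3 place the qualifying polysomnography before the invitation to take part, so a candidate's baseline AHI, the primary variable, is already known. Several exclusion criteria in 2.4, such as alcohol use or drug treatment, leave room for judgement. Selection of this kind cannot be identified afterwards from the trial data.

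**Blinding of staff, after entry.** Someone at the clinic has to set the device to active or sham and would therefore know the arm. If that person also gives the post-treatment questionnaires or reads recordings, the answers or readings may be influenced. The article does not separate these roles.

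The fixed block size links knowledge of past allocations to prediction of future ones, so the first issue can arise even if the list itself is kept out of sight.

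**Working it through.** **Inputs.** 36 patients, two groups, one site (2.1). 9 blocks of 4, size disclosed (2.6). SD of 20 events/h and target difference of 16 events/h (2.5). Assumption: 1:1 allocation, so each block holds two patients per arm; the ratio is not stated.

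**Step 1, list size.** 9 × 4 = 36, which agrees with Study design.

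**Step 2, assignments fixed with certainty.** A 2:2 block has 6 equally likely orders: AABB, ABAB, ABBA and their mirror images. An assignment is determined once one arm has used both its places.
- AABB type (2 of 6 orders): positions 3 and 4 are determined, so 2.
- ABAB and ABBA types (4 of 6 orders): only position 4 is determined, so 1.
- Mean per block: (2 × 2 + 4 × 1)/6 = 8/6 = 4/3.
- Over the trial: 9 × 4/3 = 12 of 36, or 33%. The last patient of each block gives 9 of these; the third patient, in one third of blocks, gives the other 3.

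**Step 3, best guess.** Always guess the arm with more places left in the block.
- Position 1: 1/2.
- Position 2: 2/3, because two of the three remaining places belong to the other arm.
- Position 3: 1/3 × 1 + 2/3 × 1/2 = 2/3.
- Position 4: 1.
- Sum per block: 1/2 + 2/3 + 2/3 + 1 = 17/6.
- Over the trial: 9 × 17/6 = 25.5 of 36, or 70.8%, against 18 of 36 (50%) with no information.

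**Step 4, how much is due to the block size?** The same enumeration for other fixed sizes:

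| Fixed block | Determined | Best guess correct |
|---|---|---|
| 4 | 33.3% | 70.8% |
| 6 | 25.0% | 68.3% |
| 8 | 20.0% | 66.6% |

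A larger fixed block helps only a little. Keeping list and allocation history away from the enrolling person is the main protection.

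**Step 5, conditional upper bound.** If the enrolling person reads the list directly, 36 of 36 assignments are known.

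**Step 6, sensitivity at this size (illustration only).** With 36/2 = 18 per arm, exchanging one patient for another whose AHI differs by one SD moves that arm's mean by 20/18 = 1.1 events/h. Three such exchanges in the same direction move it by 3 × 20/18 = 3.3 events/h, and 3.3/16 = 21% of the target difference. The planned pre/post comparison would absorb part of a shift in baseline AHI. It would not remove selection on characteristics that affect the response.

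**The case against.** The strongest reply is that this is a condensed article. Custody of the list, envelopes and the roles that are blinded are details commonly left to the full protocol, which Section 5 says is publicly accessible through the registry. An independent colleague reading out the next line on request would also fit the sentence in 2.6. The percentages apply only to someone who knows the earlier allocations, and they become selection bias only if that person enrols or informs whoever does. The AHI threshold of 15 events/h limits discretion at entry.

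Much of this stands. A reader might infer that the list is open and every assignment known in advance. The article does not call it open or say that the enrolling person sees it, so that case is only a possibility. A reader might also infer that the laser operator measures the outcomes and that blinding is therefore broken. The sentence on who administers data sits in the Epworth section, names the investigators in the plural, and says nothing about reading polysomnography or FMD. It shows possible overlap within the author team and no more. Nor does block size undo the guide-light sham given to participants; the exposure is among staff.

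What the reply does not remove is that 2.6 itself states the mechanism: a list made in advance, one fixed and disclosed block size, and consultation at entry. The predictability follows from that text and does not rest on silence alone.

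**Conclusion.** The point holds in a limited form. As stated, the procedure is predictable to anyone at the clinic who knows the earlier allocations: on average 12 of 36 assignments are certain and 70.8% are guessable, against 50%. This rests on 2:2 blocks and on the inference that whoever sets the laser knows the arm. That all 36 are known is conditional on the enrolling person seeing the list, which the article neither states nor rules out. The documents do not show that concealment or blinding has failed.

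Staff blinding is a separate and weaker point: the article calls the study blind without tying that to roles, and it does not keep treatment apart from assessment. Because recruitment has not begun and the remedy needs no extra staff, the change is a cheap improvement.

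**What to change.** Before the first patient:

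1. Regenerate the list with randomly varying block sizes and do not disclose the sizes.
2. Have it held by an existing team member who does not enrol, treat or assess, and say so in 2.6.
3. Release each assignment only after consent, baseline polysomnography and eligibility are recorded, through sequentially numbered, opaque, sealed envelopes or a web allocation tool, and only to the laser operator.
4. As a separate blinding measure, state who is blinded, keep the operator from administering the post-treatment questionnaires, and score polysomnography and FMD files under a coded ID.

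The costs are modest. Section 5 sends any modification to the ethics committee as an amendment and an updated version to the registry. Splitting the roles needs some scheduling. With varying blocks the final block may be incomplete, so the arms could differ slightly, by at most half the size of that block.
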